### Adapting the Mobile NAS Tool for High-Risk Pregnant Women

All videos in the existing modules for NICU providers have a script, with different content covered in each video. We will modify these modules (eg, titles, scripts, and content reading levels) to increase their relevance for high-risk pregnant women and for nonexperts. We expect that the adaption process will require (1) the removal of existing educational modules that are not appropriate for at-risk pregnant women (eg, *Epidemiology and Pathophysiology of NAS*), (2) reduction of video lengths, and (3) development of modules based on qualitative findings that are appropriate for high-risk pregnant women (eg, ESC-based caregiving skills for mothers, postpartum maternal resources, preparing for hospital length of stay, and preparing for possibly experiencing health care stigma). For example, one existing module is titled *Epidemiology and Pathophysiology of NAS*, which provides considerable detail and medical terminology. We expect that this module will need to be substantially reduced and only include a brief overview of this topic in a way that is appropriate for at-risk pregnant women. We also expect that the adapted tool will include brand-new educational modules and accompanying videos that visually demonstrate ESC-based caregiving skills that are known to soothe a NAS-affected newborn and prevent further complications. We expect that the total number of modules for perinatal women will not exceed 6.

After this initial process of modification, the modules will be uploaded to a private account on YouTube, and all participating individuals (ie, NAS providers and mothers with NAS-affected babies) will be given free web access (via a YouTube link) to the existing modules and will have the opportunity to review the existing content before providing feedback on further necessary changes and modifications. They will be asked to provide their opinion on the relevance of a new audience (pregnant women in treatment for OUD). Once semistructured interviews are completed and common themes are analyzed using qualitative description methodology, we will schedule a mini conference with the participants of this study stage (ie, NAS care experts and mothers with NAS-affected babies) to discuss the interpretation of the qualitative findings and double check for consistency that the planned adaptation of the mobile NAS tool matches what the participants tried to convey.

Although findings will ultimately guide the adaptation of the existing mobile NAS tool for high-risk pregnant women, the skills training in the adapted tool will be largely based on elements of ESC. Therefore, we anticipate that the NAS mobile tool intervention will incorporate nonintrusive caregiving skills and strategies that encompass providing a low-stimulating environment (eg, dimmed light and low noise), swaddling, continuous comfort and contact with the caregiver, skin-to-skin contact, frequent feeding, and novel components identified in the interviews.

### Stage 1: Adaptation of the Mobile NAS Instructional Tool for Pregnant Women at Risk for Having Newborns With NAS

#### Setting and Data Collection

We will recruit 10 pregnant and postpartum women from 2 locations: a regional health district’s opioid treatment program and local recovery center to participate in the semistructured interviews. Recruitment materials with contact information for study staff and a link to a brief information statement that describes the screening process and eligibility requirements will be distributed to the 2 programs via email and presented at staff meetings to recruit the 10 pregnant and/or postpartum participants. At least 10 NAS care experts (broadly defined as any person providing NAS services such as, but not limited to, nurses, social workers, obstetricians and gynecologists, and neonatologists) will also be identified and contacted from existing partnerships with local and national hospitals. After a verbal or PowerPoint description of the adapted module topics and content is provided and participants have a chance to ask questions, we will ask participants to provide feedback on the module topics and content (eg, “What do you think of the modules?” “Do you think you could use it with relative ease? What are any challenges to using it?” “Are any topics missing from the modules? “Do you think this would help you care for a baby with Neonatal Abstinence Syndrome after birth? If yes, how? If no, what could improve it?” “What do you think we should add to this study?” “Any additional thoughts and suggestions about the modules?”). Each participant who completes the interview will receive a US $25 Amazon e-gift card for their time and an additional US $25 Amazon gift card for participation in a miniconference to discuss qualitative findings. All interviews will be conducted via video or phone conferences.

#### Inclusion Criteria

Eligibility criteria were selected to allow for an accurate assessment of challenges to NAS care and necessary evidence-based skills to care for NAS-affected newborns, while maximizing generalizability of results. Inclusion criteria for NAS care experts are (1) NAS providers with significant expertise in NAS care, (2) age >18 years, and (3) ability to speak and understand English. The inclusion criteria for pregnant and postpartum participants are (1) a pregnant woman currently in OAT for OUD or a postpartum woman who has experience caring for NAS-affected newborns, (2) age >18 years, and (3) ability to speak and understand English. Participants not meeting the eligibility criteria will be excluded.

#### Data Analysis

All interviews will be digitally audio recorded and then transcribed verbatim by a professional transcriptionist. The deidentified interview transcriptions will be uploaded into NVivo version 11, a software program produced by QSR International for qualitative research. The qualitative description methodology described by Schreier [26] will be used to analyze the data. A qualitative description methodology is used when the goal is to summarize descriptions of events or experiences in a way that depicts the perspectives of the participants [27,28]. Common themes will be identified in the data (transcripts) to provide definitions and details of the most prominent ideas provided by participants’ responses. The qualitative description methodology will involve combing concept-driven and data-driven analysis approaches to the text; reliability will be addressed by the process of having each researcher (ie, principal investigator, research coordinator, and research team) initially review and analyze the data before each meeting and then comparing consistency of agreement between the researchers, and validity will be addressed by considering the applicability of the themes when compared with participants’ responses. An audit trail will be kept throughout the analysis process to document decisions and next steps.

### Stage 2: Usability, Acceptability, and Feasibility of the Adapted NAS Tool

#### Data Collection and Outcomes

We will recruit 10 pregnant women receiving OAT from 2 locations: a regional health district’s opioid treatment program and a local recovery center to participate in the survey, as described earlier in stage 1. Consented participants will be asked to review the adapted content (via a private YouTube link) before completing the surveys. Once they review the adapted modules, they will be directed to complete a Research Electronic Data Capture survey that will assess several measures. Acceptability will be examined by the 8-item Client Satisfaction Questionnaire (CSQ-8) to rate the overall satisfaction with the adapted NAS tool [29]. Usability will be assessed using the 10-item Systems Usability Scale (SUS), in which they are asked to answer questions about a mobile app (eg, “I think that I would need the support of a technical person to be able to use this app”) [30,31]. To assess feasibility, a measure of utility will be assessed via several questions (eg, “To what extent do you expect to be able to incorporate the NAS caregiving tool in your daily activities during pregnancy and postpartum?”), tracking how many times participants referred to specific modules within the mobile tool, and open-ended questions that ask participants to comment on the feasibility of this tool along with overall impressions and comments on the tool (survey details are given in Tables 1 and 2). Participants will receive a US $25 e-gift card for their time.

**Table 1 table1:** Measures and timing of data collection for stage 3 randomized controlled trial.

Outcomes		Baseline (during the third trimester)	4, 8, and 12 weeks postpartum
**Demographic characteristics**			
	Age	✓^a^	N/A^b^
	Education level	✓	N/A
	Marital status	✓	N/A
	Time in OAT^c^ program	✓	N/A
	Number and age of living children	✓	N/A
	Employment	✓	N/A
**Baseline characteristics**			
	Addiction Severity Index-Lite	✓	N/A
	Maternal Antenatal Attachment Scale	✓	N/A
**Outcome measures**			
	Addiction Severity Index-Lite	✓	✓
	Maternal Postpartum Attachment Scale	N/A	✓
	Birth Satisfaction Scale-Revised	N/A	✓
	Patient Health Questionnaire-9	N/A	✓
	Parenting Stress Index	N/A	✓
	Client Satisfaction Questionnaire-8	N/A	✓
	System Usability Scale	N/A	✓
	Length of hospital stay for newborn	N/A	✓
	Newborn hospital readmission	N/A	✓
	Breastfeeding initiation and duration	N/A	✓
	Maternal OAT continuation and relapse	N/A	✓
	Frequency of NAS^d^ tool use (weekly)	✓	✓

^a^Data collected.

^b^N/A: not applicable.

^c^OAT: opioid agonist therapy.

^d^NAS: neonatal abstinence syndrome.

**Table 2 table2:** Outcomes and description of measures.

Study stage and outcome			Study design		Description of measures
**Stage 1: NAS^a^ tool adaptation**					
	Tool adaptation	Semistructured interviews		Semistructured interviews with a panel of NAS care experts and mothers with NAS-affected newborns until we reach saturation (expected n=10) to document their perspectives and gather their recommendations on the care of newborns with NAS.	
**Stage 2:** **Usability, acceptability, and feasibility of the adapted NAS tool**					
	Usability	Survey		Participants will complete a 10-item SUS^b^, in which they are asked to answer questions about a mobile app (eg, “I think that I would need the support of a technical person to be able to use this app”) using a 5-point Likert scale, ranging from strongly disagree to strongly agree. The SUS is currently the industry standard for evaluation of a wide variety of products and services such as software, mobile devices, websites, and apps [30,31]. The SUS has been shown to successfully differentiate between usable and unusable systems, and it can be used in small samples with reliable results [30,31].	
	Acceptability	Survey		Acceptability will be examined by the CSQ-8^c^ to rate the overall satisfaction with the adapted NAS tool [29]. CSQ-8 is a validated questionnaire measuring satisfaction with health services (eg, “How would you rate the quality of care your received?”) that has been translated in more than 30 languages [29,32,33]. Possible total scores on CSQ-8 range from 8 to 32, with higher scores (>23) indicating greater satisfaction with health services.	
	Feasibility	Survey		To assess feasibility, a measure of utility will be assessed (eg, “To what extent do you expect to be able to incorporate the NAS caregiving tool in your daily activities during pregnancy and postpartum?”), tracking how many times participants referred to specific modules within the mobile tool and open-ended questions that ask participants to comment on feasibility of this tool along with overall impressions and comments.	
**Stage 3:** **Clinical trial comparing NAS tool with usual care**					
	Demographic characteristics	Randomized clinical trial		Demographics and baseline characteristics, such as age, education, marital status, time in the OAT^d^ program, number and age of living children, employment, and ASI-Lite^e^, will be collected at the start of the study to describe the sample and to serve as control variables when comparing groups on the outcomes.	
	Maternal drug use and relapse	Randomized clinical trial		Maternal drug use and relapse will be assessed via ASI-Lite, a standardized semistructured clinical interview that offers clinical information and assesses severity profiles in the following domains: medical, employment, alcohol, drug, psychological, legal, and family and social [34]. It has been shown to have adequate to good internal consistency, good test-retest reliability, independence across the domain composite scores, and agreement with the longer version of the ASI-Lite [34].	
	OAT continuation	Randomized clinical trial		OAT continuation will be assessed via a single question (“Are you currently receiving OAT (Yes or No)? Please explain”).	
	Length of newborn hospital stay and readmission	Randomized clinical trial		These will be determined by single questions: length of newborn hospital stay (“how many days did your newborn stay in the hospital”) and newborn hospital readmission (“has your newborn been readmitted to the hospital for any reason after discharge? If yes, how many times? Please list reasons for each readmission”).	
	Perinatal maternal-fetal attachment	Randomized clinical trial		Prenatal maternal-fetal attachment will be measured with the Maternal Antenatal Attachment Scale [35,36], a reliable and validated 19-item measure of maternal-fetal attachment that includes several response formats and assesses 2 dimensions: 1) quality of attachment (11 items) and 2) intensity of preoccupation (8 items). The total scores range from 19 to 95, with higher scores indicating a higher level of attachment to the fetus [35-39]. Maternal-newborn bonding will be measured via MPAS^f^ [40,41]. It consists of 19 items assessing 3 dimensions: *pleasure in interaction with the infant* (5 items), *absence of hostility toward the infant* (5 items), and *quality of mother-infant attachment* (9 items). Response categories range from 2-, 3-, 4-, to 5-point scales, for different items. The total score ranges from 19 to 95, with higher scores indicating higher maternal postpartum attachment to the baby. The MPAS has been found to have an acceptable level of reliability (Cronbach α ranging from .75 to .79; test-retest reliability *r*=0.86; *P*<.001) [37,40,41].	
	Maternal birth experience	Randomized clinical trial		The Birth Satisfaction Scale-Revised, a 10-item, Likert-type birth satisfaction questionnaire that measures experiences of childbearing, stress, quality of care, and women’s attributes, was psychometrically validated in the United States by our research team [42-44]. Its response categories range from 1=strongly disagree to 5=strongly agree, with higher scores indicating higher birth satisfaction.	
	Maternal Depression	Randomized clinical trial		Assess via the PHQ-9^g^, a psychometrically validated 9-item measure used to assess depression in a variety of populations [45-47]. The PHQ-9 asks participants to report on the degree they were bothered by 9 symptoms over the past 2 weeks (ie, “little interest or pleasure in doing things” and “feeling down, depressed, or hopeless”), with response categories ranging from 0=not at all to 3=nearly every day and higher scores indicating greater levels of depression symptomology.	
	Maternal stress	Randomized clinical trial		PSI^h^ measures parental stress associated with the perception of having a difficult child or a dysfunctional parent-child relationship and consists of 36 items that are rated on a 5-point Likert scale (from 1=strongly agree to 5=strongly disagree), with higher scores indicative of less total stress [48]. PSI has been shown to possess good psychometric properties and has been validated in numerous samples, including high-risk families [49]. It includes parental distress, parent-child dysfunctional interaction, and difficult child subscales, all of which will be considered individually. The child and parent domains can and will be combined to form a total stress scale score.	
	Breastfeeding	Randomized clinical trial		Assessed via several questions “Are you currently breastfeeding? If yes, ‘How often do you breastfeed your baby?’, if no, ‘How long did you breastfeed your baby.’”	
	Frequency of NAS tool use	Randomized clinical trial		Throughout their third trimester and postpartum, we will also send participants a brief weekly web-based survey link asking about the previous week’s frequency of use of the adapted mobile NAS tool and which specific modules participants viewed most, if any, to track weekly frequency of use and preference of modules.	

^a^NAS: neonatal abstinence syndrome.

^b^SUS: Systems Usability Scale.

^c^CSQ-8: 8-item Client Satisfaction Questionnaire.

^d^OAT: opioid agonist therapy.

^e^ASI-Lite: Addiction Severity Index-Lite.

^f^MPAS: Maternal Postpartum Attachment Scale.

^g^PHQ-9: 9-item Patient Health Questionnaire

^h^PSI: Parenting Stress Index short form.

#### Inclusion Criteria

Participants will be pregnant women (1) who are in the third trimester currently in OAT treatment for OUD, (2) aged >18 years, and (3) who are able to speak and understand English. Participants who did not meet the eligibility criteria will be excluded.

#### Data Analysis

Descriptive analyses will be conducted using percentages, means, and SDs to describe the feasibility and acceptability of the adapted mobile NAS tool for pregnant women receiving OAT. All descriptive analyses will be conducted using STATA version 14.2. This developmental stage will not require limited inferential tests because the sample sizes are small, and the qualitative work will be the primary driver of the modifications to be made and eventually tested in a randomized trial in stage 3.

### Stage 3: Clinical Trial to Test the NAS Instructional Tool Versus Usual Care to Potentially Improve Postpartum Maternal-Newborn Health Outcomes

#### Data Collection and Inclusion Criteria

Similar to previous stages, we will recruit 30 pregnant women in their third trimester from the same 2 treatment centers to participate in stage 3 of the study. After a brief phone screening, eligible participants will then be consented and randomized 1:1 into either the intervention condition (ie, adapted NAS tool intervention, as given in the *Study Intervention* section) or the control condition (ie, treatment as usual [TAU], as given in the *Study Intervention* section). Participants will be asked to provide demographic and baseline information at this point. Women in the intervention condition will go through the mobile-based NAS instructional tool at least once during pregnancy, with their choice of going through the modules gradually while waiting at the OAT clinic to receive their dose or by scheduling a time to review the modules with research staff outside of the clinic (either at university offices or via a video conference). Participants will be met with a research assistant who will provide them with an iPad and access to the modules (via a private YouTube link), and the research assistant will be available for any questions throughout the review. Participants will be able to create a YouTube account on the iPad and will be able to access, skip, pause, and continue the modules at any time during the duration of the study through the 12-week follow-up period (ie, access after giving birth as well). They will also be able to post questions or comments under private YouTube videos for research staff to see and address. Each participant will also be scheduled for the 3 follow-up appointments (at 4, 8, and 12 weeks postpartum). Follow-up appointments will consist of filling out surveys (Table 1). Participants will be able to complete the survey on their phones or iPads. For completing all study appointments, participants will receive a total of US $125 in Amazon e-gift cards (US $25 after providing demographic and baseline information, US $25 after reviewing the modules with a research assistant, and an additional US $25 Amazon gift card for each of the 3 follow-ups). The inclusion criteria are as follows: (1) a pregnant woman currently undergoing OAT treatment for OUD, (2) age >18 years, and (3) ability to speak and understand English. Exclusion criteria are as follows: recurring (eg, daily or almost daily) thoughts of harming themselves or others in the past 2 weeks.

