
#### Study Intervention

TAU pregnant women in this condition will receive care as usual, which involves continued enrollment in OAT and continued obstetric care. We will also provide them with a printed handout containing information on NAS and local resources. This level of information meets or exceeds what most mothers in this situation usually receive. Participants in the TAU condition will not receive iPads with accompanying modules; however, the handout constitutes more information than they normally receive.

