
#### Data Analysis

Means (SDs) will be calculated for continuous variables, and percentages will be calculated for categorical variables for the 2 groups (intervention group and TAU group) at each assessment. Demographic and baseline characteristics will be tested across intervention versus TAU via independent-samples *t* tests and one-way analysis of variance (for continuous variables) and chi-square tests (for categorical variables). Generalized estimating equations will be used to analyze the primary longitudinal outcomes of maternal drug relapse and OAT continuation and secondary outcomes and to control for any baseline demographic differences across groups, where intervention versus TAU remains as the primary independent variable. Analyses will control for baseline and demographic outcomes and time. All inferential results will be presented as odds ratios with 95% CIs for binary outcomes and unstandardized regression coefficients with 95% CIs for continuous outcomes. We will use an α error rate of .05 as the threshold for statistical significance. All analyses will be conducted using STATA version 14.2.

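### The stated enrolment order puts randomization before baseline data, so participant-reported covariates could be coloured by knowledge of the arm

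*Protocol article*

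**What the plan says.** All references are to the protocol article.

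- **Order of steps** (Stage 3, Data Collection and Inclusion Criteria). After a phone screen, "eligible participants will then be consented and randomized 1:1 into either the intervention condition" or the control condition. The next sentence is: "Participants will be asked to provide demographic and baseline information at this point". The trial size is given in the same section: "we will recruit 30 pregnant women in their third trimester", which is 15 per arm at 1:1.
- **Other mentions of baseline timing.** The Table 1 column heading places baseline in the third trimester, and Table 2 places it at the start of the study. Neither says whether it comes before or after randomization.
- **Recognizability of the arms** (Study Intervention). "Participants in the TAU condition will not receive iPads with accompanying modules"; they get a printed handout. The time at which a woman learns her arm is not stated.
- **Baseline instruments.** Table 1 lists ASI-Lite and the Maternal Antenatal Attachment Scale as baseline characteristics. On the first, Table 2 says "Maternal drug use and relapse will be assessed via ASI-Lite, a standardized semistructured clinical interview". On the second, it says "Prenatal maternal-fetal attachment will be measured with the Maternal Antenatal Attachment Scale".
- **Use in the analysis.** Table 2 says that the demographic items and ASI-Lite are collected to describe the sample and "to serve as control variables when comparing groups on the outcomes". The Stage 3 Data Analysis section adds: "Analyses will control for baseline and demographic outcomes and time".

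**The concern.** A covariate can safely be adjusted for in a randomized comparison when allocation cannot have affected it. Measuring it before randomization guarantees that. Measuring it afterwards, in a trial where women can recognize their arm, does not.

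The covariate that matters most is ASI-Lite. Its content comes from the woman's own account, it is a named control variable, and the same instrument supplies the primary relapse outcome. A woman who knows she has been assigned the tool, or has missed it, might describe her drug use differently. The same could happen with the attachment scale.

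Two things are at stake:

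1. **Bias in the adjusted effect.** If knowledge of the arm moves the reported baseline, the generalized estimating equations treat that movement as a pre-existing difference and correct the treatment effect for it.
2. **Missing covariates after allocation.** A woman who skips baseline once she knows her arm but still attends follow-up has outcomes and no covariates. Unless her values are imputed, the adjusted model leaves her out.

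The planned tests of baseline characteristics across arms would not settle the matter. A difference could be chance, or it could reflect knowledge of the arm.

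**Working it through.** The article gives no figure for this point, so there is nothing to reproduce. The check has three parts.

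**1. Order of steps.** The Stage 3 text runs: phone screen, consent, randomization, demographic and baseline data. No other section puts baseline earlier, and none describes concealing the arm until baseline is finished. Table 1 also ticks weekly frequency of tool use in the baseline column. That may only reflect the weekly survey in the third trimester, but it does not correct the order.

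**2. Which covariates could move.**

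| Baseline item | Named control variable in Table 2? | Could knowledge of the arm alter the answer? |
|---|---|---|
| Age, education, marital status, time in OAT, children, employment | Yes | Unlikely |
| ASI-Lite | Yes | Possible |
| Maternal Antenatal Attachment Scale | No; only if the general reference to baseline in Data Analysis includes it | Possible |

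**3. Size for a continuous outcome.** Inputs: 15 per arm (30 at 1:1) and alpha .05, both from the article, with alpha taken as two-sided. The slope b of outcome on baseline and the shift s in reported baseline (in SD, one arm only) are assumptions, because the article gives neither.

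Let B be the true baseline, X = B + s × arm the reported one, and Y = b × B + error, with no treatment effect. Substituting B = X − s × arm gives

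Y = b × X − (b × s) × arm + error.

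So the adjusted arm effect is −b × s although the true effect is zero. With b = 0.5:

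- s = 0.2: −0.5 × 0.2 = −0.10 SD
- s = 0.4: −0.5 × 0.4 = −0.20 SD

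The signs are for an upward shift in the intervention arm; a downward shift reverses them.

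A simulation of baseline-adjusted linear regression (15 per arm, true effect zero, 20,000 runs per setting, b equal to the baseline-outcome correlation) agrees with the formula:

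| b | s | Simulated bias (SD) | −b × s | Type I error |
|---|---|---|---|---|
| 0.3 | 0 | −0.001 | 0 | 0.049 |
| 0.3 | 0.2 | −0.063 | −0.06 | 0.051 |
| 0.3 | 0.5 | −0.150 | −0.15 | 0.064 |
| 0.5 | 0 | 0.000 | 0 | 0.048 |
| 0.5 | 0.2 | −0.097 | −0.10 | 0.062 |
| 0.5 | 0.5 | −0.252 | −0.25 | 0.112 |
| 0.7 | 0 | 0.002 | 0 | 0.050 |
| 0.7 | 0.2 | −0.142 | −0.14 | 0.082 |
| 0.7 | 0.5 | −0.347 | −0.35 | 0.232 |

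The rows with s = 0 represent baseline taken before the arm is known: bias is essentially zero and type I error is nominal.

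For scale, with b = 0.5 the standard error of the adjusted difference is about √(2/15) × √(1 − 0.25) = 0.365 × 0.866 = 0.316 SD. A bias of 0.10 to 0.20 SD is therefore about 0.32 to 0.63 of one standard error.

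**Missing covariates.** Each woman who stays in follow-up without baseline data is 1/15 = 6.7% of her arm.

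**The case against.** The strongest reply is that the text is a short narrative in a condensed article. Its wording on when baseline is collected could mean the same enrolment contact, without fixing the order within it. The bias also needs the woman to know her arm when she answers, and the article does not say when she is told. Baseline appears to come before the modules, with separate payments for each, so only anticipation could act, not the tool itself. The trial is described as exploratory, and the article concedes that its size limits conclusions on effectiveness.

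Most of this stands as a limit on strength. It does not remove the point, because the only order given places randomization first and nothing in the text prevents disclosure before baseline.

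Four stronger readings are tempting but not supported:

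- **That the baselines will be contaminated.** The time of disclosure is not stated, so the documents show only that the written order allows it.
- **That the attachment scale is certainly a covariate.** Table 2 does not name it as a control variable, and the general wording in Data Analysis leaves it open.
- **That women who leave on learning they are controls are lost because of this order.** A woman who leaves before follow-up has no outcomes at 4, 8 or 12 weeks under either order. Reordering preserves covariates only for those who skip baseline but remain in follow-up. Even there, exclusion from the model presumes that missing covariates are not imputed, and how missing data are handled may be left to the analysis plan.
- **That the primary results are biased by 0.1 to 0.2 SD.** Slope and shift are assumed. OAT continuation is a yes/no item to be reported as an odds ratio, a scale on which this formula does not apply.

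**Conclusion.** The concern holds as a risk that the stated procedure permits. Randomization precedes baseline in the only passage that gives the order, the arms are recognizable, and no safeguard on disclosure is described. ASI-Lite is the main exposure, because it is both a named control variable and the primary relapse instrument. The Maternal Antenatal Attachment Scale is a second one only if the baseline adjustment includes it.

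The size cannot be derived from the article. The 0.1 to 0.2 SD range shows the order of magnitude for a continuous outcome under the assumed slope and shift; for binary outcomes no size has been derived. At a weak baseline-outcome correlation the effect on type I error is small, and it becomes large only at the most extreme pair of values tried.

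Severity is moderate. The point merits action because the remedy is nearly free and an uncontaminated baseline cannot be recovered once women have enrolled.

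**What to change.** Reword the enrolment text in Stage 3, Data Collection and Inclusion Criteria, so that the order is: phone screen; consent; all baseline measures (demographics, ASI-Lite, Maternal Antenatal Attachment Scale); randomization; disclosure of the arm. If randomization must be run earlier for practical reasons, state that the allocation is withheld from the woman and from the staff collecting baseline until the baseline record is marked complete.

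The cost is the rewording and the order of steps within enrolment; questionnaires, staff and payments stay the same. The Results section places the Stage 3 trial in late 2022, after the article's reporting date of January 2021, so the plan left time to make the change before enrolment. If practice already follows this order, correcting the sentence is enough.
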